### Recruitment and Screening

We began recruiting participants in July 2022. Older adults with self-reported ECD and CP are recruited from MGH clinics (Pain Clinic, Memory Unit, Multicultural Alzheimer Prevention Program, and Geriatric Medicine Unit) through multidisciplinary clinician–referred individuals (ie, pain psychologists and geriatricians), by distributing our IRB-approved study flyer through hospital-wide emails via the Rally Research web-based platform, and via social media. Our entirely web-based trial enables us to recruit from the local community and nationally (eg, memory cafes and organizations for older adults). Research assistants log all incoming referred individuals in a REDCap (Research Electronic Data Capture; Vanderbilt University) database (for storing protected health information) and a recruitment log (for tracking the flow of referred individuals and contact attempts). Research assistants conduct individual phone screening to provide study details and determine eligibility. We embedded an R code in the recruitment flyer that allows referred individuals to complete the initial eligibility screening on their own via a simple REDCap checklist. Research assistants answer questions about the study and collect information about availability with all eligible referred individuals. Self-reported CP and ECD are confirmed by referring clinicians and a review of the patient’s medical records when available. Referred individuals that do not meet the study criteria are offered a resource sheet for CP and ECD developed for older patients. The principal investigator confirms all the screening before enrollment and consults with the interdisciplinary team of psychologists, neuropsychologists, and geriatricians as needed.

### Inclusion of Ethnoracially Diverse Older Adults

Our team developed strategies to increase the recruitment and retention of ethnoracially diverse older adults. We included recruitment sites within our institution that serve ethnoracially diverse older patients, including the Multicultural Alzheimer Prevention Program and Senior Health. We have consulted with the MGH Community Access, Recruitment, and Engagement Center about a variety of outreach strategies, which include community talks and presentations, tabling, health fairs, individual meetings, and events. We are prioritizing the recruitment of ethnoracially diverse older adults by using recommendations from the literature. These include, but are not limited to, the following: (1) developing culturally sensitive and inclusive study materials, (2) exercising flexibility in scheduling and emphasizing study resources to reduce barriers to participation, (3) asking trusted clinicians (ie, physicians, nurses, social workers, psychologists, and medical assistants) and community members to introduce the study to patients, (4) training the staff on culturally sensitive communication and recruitment strategies that focus on building trust and rapport, (5) prioritizing approaching all ethnoracially diverse older patients who present to recruitment sources as feasible, (6) inviting family into the decision-making process and to support participation (eg, reinforce attendance and troubleshoot technology), (7) addressing the stigma associated with CP and ECD, (8) providing tablets and smartphones with data plans to older adults who do not have them, (9) providing one-on-one training to learn technology, and (10) increasing the diversity of study staff [41-45]. If needed, we will expand recruitment to satellite clinics (MGH Dimmock, Chelsea, Revere, and Waltham) and the Boston Medical Center Pain Clinic.

### Assessments and Enrollment

#### Informed Consent and Mailing of Study Materials

After recruiting at least 8 eligible participants (ie, the minimum threshold to start forming a round of groups), research assistants contact each participant to coordinate the informed consent process and mailing of study procedures. A total of 3 weeks before the first AB or HEP session, research assistants conduct 30-minute Zoom (Zoom Video Communications) meetings with participants to: (1) review and sign the electronic consent form, (2) test Zoom and eliminate barriers to web-based participation, (3) download the Timed Walk app [46] (to self-administer the 6-min walk test), (4) schedule the baseline assessments, (5) assess delivery preferences (timing, email, or SMS text) for receiving daily study reminders, (6) collect an address to mail the study materials, and (7) identify a friend or family member to troubleshoot technology if needed. After consent, a research assistant mails the following to each participant: (1) a study welcome letter, (2) a complementary pen and magnet with the study logo and contact information, (3) Repeatable Battery for the Assessment of Neuropsychological Status (RBANS) Update [47] cognitive assessment forms, and (4) a wrist-worn ActiGraph wGT3X-BT (ActiGraph LLC) [48,49] watch and materials (user-friendly instructions and charger) for blinded step count assessment. We provide tablets (to sync watches, respond to surveys, and attend the AB or HEP sessions) to promote equitable participation of older adults who do not own these devices. These participants receive an additional tutorial with a research assistant to set up their tablet. Participants are instructed to leave the study package unopened until the group, baseline assessment Zoom session. So far, all participants have provided informed consent, and all study procedures have been conducted in accordance with our IRB-approved protocol.

#### Assessments

We selected measures based on the Initiative of Methods, Measurement, and Pain Assessment in Clinical Trials [50] and International Classification of Functioning [51] guidelines for CP clinical trials, our conceptual model [10,52-55], and previous AB studies [28,30]. All outcome measures are assessed at baseline, after the intervention, and at 6-month follow-up. Table 1 reports details about the measures, organized according to construct.

**Table 1 table1:** Study measures and constructs.

Categories and subcategories		Time points
**Demographic factors**		
	Date of birth, gender, weight, height, handedness, race or ethnicity, marital status, education level, employment status, income, and concurrent medical therapies	Baseline
**Clinical factors**		
	Type of ECD^a^ (subjective or objective), pain diagnoses, pain location, length of chronic pain, comorbid medical conditions, current and history of mental health conditions, current pain medication, current memory medication, and current treatments (eg, physiotherapy and occupational therapy)	Baseline
**Coprimary outcomes**		
	Accelerometer (wrist-worn ActiGraph wGT3X-BT)—measures 7-d average step count [48,49]	Baseline, after the intervention, and 6-mo follow-up
	6-min walk test using the Timed Walk app—measures the distance walked in meters at a fast pace for 6 min using smartphone GPS [46]	Baseline, after the intervention, and 6-mo follow-up
	PROMIS^b^ (version 1.2.8b)—measures the level of difficulty with daily function [56,57]	Baseline, after the intervention, and 6-mo follow-up
**Secondary outcomes**		
	Repeatable Battery for the Assessment of Neuropsychological Status—measures 5 cognitive domains (immediate memory, visuospatial and constructional, language, attention, and delayed memory) and global cognition [47]	Baseline, after the intervention, and 6-mo follow-up
	Everyday Cognition Scale—measures self-reported cognitive functioning by comparing current performance on cognitive tasks with that a decade ago [58]	Baseline, after the intervention, and 6-mo follow-up
	PROMIS Depression (version 1.0.8b)—measures negative mood, views of self, engagement in daily living, and social components [59]	Baseline, after the intervention, and 6-mo follow-up
	PROMIS Anxiety (version 1.08a)—measures fear, worry, hyperarousal, and somatic symptoms [59]	Baseline, after the intervention, and 6-mo follow-up
	Numerical Rating Scale—measures pain intensity at rest and during activity during the past week [60]	Baseline, after the intervention, and 6-mo follow-up
	PROMIS Pain Interference (version 1.0.8a)—measures the consequences of pain on relevant aspects of life, including social, cognitive, emotional, physical, and recreational activities [56,61]	Baseline, after the intervention, and 6-mo follow-up
	The Pain, Enjoyment of Life, and General Activity Scale [62]—measures pain intensity and pain interference in the past week	Baseline, after the intervention, and 6-mo follow-up
**Mechanisms**		
	Quota-based pacing—measures the perceived use of quota-based activity pacing using a 4-item scale adapted from the Activity Pacing Questionnaire [63]	Baseline, after the intervention, and 6-mo follow-up
	Memory Compensation Questionnaire—measures the use of cognitive compensatory strategies for actual or perceived memory loss [64,65]	Baseline, after the intervention, and 6-mo follow-up
	Pain Catastrophizing Scale—measures hopelessness, helplessness, and rumination about pain [66]	Baseline, after the intervention, and 6-mo follow-up
	Tampa Kinesiophobia Scale—measures the fear of activity owing to pain or injury [67]	Baseline, after the intervention, and 6-mo follow-up
	Pain Self-Efficacy Questionnaire—measures self-efficacy for performing activities of daily living despite pain [68]	Baseline, after the intervention, and 6-mo follow-up
	Self-Compassion Scale—measures self-compassion in the face of stressors or challenges [69]	Baseline, after the intervention, and 6-mo follow-up
	Measures of Current Status—measures the ability to engage in a series of general coping skills (eg, relaxation, being aware of tension, expressing needs, confidence in coping, and assertiveness) [70]	Baseline, after the intervention, and 6-mo follow-up
	Gratitude Questionnaire—measures the ability to experience gratitude daily [71]	Baseline, after the intervention, and 6-mo follow-up
	Toronto Mindfulness Scale—measures self-reported state-level mindfulness [72]	Baseline, after the intervention, and 6-mo follow-up
**Exploratory**		
	Global Cognitive and Social Engagement—measures the perceived engagement in mentally stimulating social and cognitive activities (involving meaning, learning, challenge, and creativity) and passive activities (eg, watching television)	Baseline, after the intervention, and 6-mo follow-up
	NIH^c^ Toolbox Loneliness Fixed Form Age 18+ (version 2.0)—measures the perception that one is alone, lonely, or socially isolated from others [73]	Baseline, after the intervention, and 6-mo follow-up
	PROMIS Satisfaction with Social Roles and Activities (version 2.0.8a)—measures satisfaction with social roles and responsibilities [74]	Baseline, after the intervention, and 6-mo follow-up
	OQ^d^ Therapeutic Alliance—assesses participant perceptions about therapeutic alliance [75]	After the intervention

^a^ECD: early cognitive decline.

^b^PROMIS: Patient-Reported Outcomes Measurement Information System.

^c^NIH: National Institutes of Health.

^d^OQ: Outcome Questionnaire.

#### Self-Report Measures

Participants complete the self-report measures via the web-based REDCap platform during a 60-minute group assessment via Zoom. In our previous AB studies, we learned that group assessments allow our research assistants to efficiently provide technical support with Zoom (eg, connectivity issues) and REDCap (eg, accessing or responding to survey questions) for multiple participants simultaneously. To encourage focus and privacy during the self-reports, the Zoom host mutes all participants and asks them to use the chat or *raise hand* function for help. After completing the surveys, participants have the option of remaining on the call to receive additional technological support from the research assistants. Research assistants review all self-reports for missing data and errors that were not prevented by the REDCap response validation features.

#### ActiGraph wGT3X-BT

During the group baseline (1-2 wk before the first session), participants open their study package and place the ActiGraph watch on their nondominant wrist to measure step count. Participants are instructed to wear the ActiGraph watch daily (except when bathing) until 1 week after the intervention. Participants sync (using the CentrePoint smartphone app) the watch daily and charge weekly. The research assistants review tips to care for their ActiGraph watch, address common misconceptions (eg, no GPS tracking or on or off switch), and encourage them to contact the study staff for technical support. ActiGraph wGT3X-BT is widely used [49] to measure step count and has demonstrated validity in older adults [76]. Participants receive and wear the ActiGraph watch for 1 more week at the 6-month follow-up and return it in a prepaid envelope.

We estimate an average 7-day step count for each participant, measured by ActiGraph wGT3X-BT at baseline, after the intervention, and at 6-month follow-up using an established protocol [30,34,35]. First, we exclude nonwear (no data) or invalid wear days, which is defined as less than 7 hours of wear time during waking hours [77,78]. Next, we exclude the highest and lowest step-total days to prevent very active or inactive days from skewing average step counts. Finally, we average the remaining valid days (minimum days to calculate average count=3).

#### RBANS Assessment

After the group assessment, participants complete an individual 30-minute RBANS cognitive assessment with trained clinicians via Zoom. The clinician confirms that participants have received the testing materials (RBANS figure copy and coding sheets) and have secured an ideal testing environment. This includes (1) stable connectivity, (2) full-screen Zoom on a tablet or laptop (no smartphone), (3) clear audio, (4) no environmental (phone is silenced and no background activity) distractions, (5) proper lighting, (6) flat surface to write, (7) screen-sharing capability, and (8) privacy for the duration of the test. Following the established telepractice guidelines [79], the clinician shares their screen to show the stimulus book, takes screenshots for scoring, and instructs participants to mail written items (figure drawing and coding) in a prepaid envelope.

#### The 6-Minute Walk Test

After completing RBANS, the clinician instructs the participant to complete the 6-minute walk test outside, on flat terrain using Timed Walk. Timed Walk is a GPS-enabled smartphone app, which enables users to measure walking distance within a fixed time frame. The 6-minute walk test performed using Timed Walk is a valid performance-based measure of physical function and presents a reliable alternative to traditional laboratory assessments [46]. The assessment period is complete once the participants call the research assistant with their 6-minute walk test score.

#### Randomization

A week before the first AB or HEP session, research assistants randomize and enroll participants via phone. Participants are randomly assigned in a 1:1 ratio to AB intervention or HEP control to ensure comparability between groups. The unblinded study biostatistician created the randomization schedule with permuted blocks of random sizes and implemented it in REDCap. Randomization is stratified according to ECD type (subjective vs mild cognitive impairment). To maintain single-arm blinding, study staff and materials refer to AB and HEP as AB1 and AB2, respectfully. Without unblinding, research assistants notify each participant about their group assignment, schedule weekly session times, and provide links to the AB or HEP websites. Research assistants review expectations for attending the group sessions, including the following: (1) timeliness, (2) quiet location, (3) respectfulness of others, (4) no multitasking, (5) wearing the watch, (6) having a pen and the manual ready, and (7) responding to daily smartphone surveys to complete home practice. The research assistant mails a printed copy of the program manual to be received by participants before the first group session. Participants in the AB arm receive a Fitbit to wear, starting after session 1 to ensure that step count assessment remains blind in both groups. Participants are considered to be enrolled after completing session 1 of the AB or HEP arms.

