**Methods:**

Participants are identified and recruited through multidisciplinary clinician–referred individuals (eg, pain psychologists and geriatricians), the Rally Research platform, social media, and community partnerships. Interested participants complete eligibility screening and electronic informed consent. Baseline assessments include self-report, performance-based measures (eg, 6-min walk test) and objective measures (eg, Repeatable Battery for the Assessment of Neuropsychological Status). Participants are mailed a wrist-worn ActiGraph device (ActiGraph LLC) to passively monitor objective function (eg, steps) during the week between the baseline assessment and the beginning of the programs, which they continue to wear throughout the programs. After baseline assessments, participants are randomized to either AB or HEP and complete 8 weekly, remote, group sessions with a Massachusetts General Hospital psychologist. The AB group receives a Fitbit (Fitbit Inc) to help reinforce increased activity. Assessments are repeated after the intervention and at the 6-month follow-up. Coprimary outcomes include multimodal physical function (self-report, performance based, and objective). Secondary outcomes are cognitive function (self-report and objective), emotional function, and pain.

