#### Data Analyses

##### Overview

Our blinded statistician will conduct all data analyses using SAS (version 9.4) [92]. We will estimate treatment-dependent changes in primary (objective, performance-based, and patient-reported physical function) and secondary outcomes (patient-reported and objective cognitive function and emotional function). We will follow the intention-to-treat principle and include all randomized participants in our primary efficacy analyses. Data will be analyzed using a shared-baseline, linear mixed model with fully unstructured covariance among repeated measures. The shared-baseline assumption reflects the true state of the population before randomization and has the benefit of adjusting for chance differences at baseline. Linear mixed models with maximum likelihood estimation are unbiased when data are missing at random, conditional on the observed data. If loss to follow-up is strongly treatment-dependent (relative risk >2), we will use perturbed multiple imputation to assess the robustness of estimates from the primary model if data were missing in not-at-random manner.

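### The stated schedule does not ensure that the 7-day baseline step count closes before randomisation and release of arm-specific materials

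*Protocol article*

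**What the plan says.** The protocol article gives the timing in several places.

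- **Informed Consent and Mailing of Study Materials:** consent is 3 weeks before session 1, and the watch is mailed afterwards. "Participants are instructed to leave the study package unopened until the group, baseline assessment Zoom session".
- **ActiGraph wGT3X-BT:** this section fixes when wear starts. "During the group baseline (1-2 wk before the first session), participants open their study package and place the ActiGraph watch on their nondominant wrist". It also defines the step outcome as a 7-day average: invalid days are dropped, then the highest and lowest days, with a minimum of 3 days for the average. It does not say which 7 days form the baseline.
- **Abstract, Methods:** the watch is worn "to passively monitor objective function (eg, steps) during the week between the baseline assessment and the beginning of the programs". The same paragraph says "After baseline assessments, participants are randomized to either AB or HEP".
- **The 6-Minute Walk Test:** "The assessment period is complete once the participants call the research assistant with their 6-minute walk test score". Completion of 7 wear days is not a condition.
- **Randomization:** "A week before the first AB or HEP session, research assistants randomize and enroll participants via phone". In the same contact participants are told their group under a masked label and given the link to their arm's website. The printed manual is to arrive before session 1. Under Treatment Arms, the website is said to carry a digital copy of the manual.
- **Improvements to AB for This Trial:** the revised AB manual presents walking as the programme's main target.
- **Data Analyses, Overview:** the primary model constrains the arms to a common baseline mean, because "The shared-baseline assumption reflects the true state of the population before randomization".

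**The concern.** A shared-baseline model is justified when baseline is measured before allocation, since the two arms then have the same expected baseline by design. If the baseline is measured, even in part, after participants know their group and can open arm-specific material, that guarantee is lost. Any difference in walking between arms during that week enters the baseline of a coprimary outcome. The model holds the baseline means equal, so it treats such a difference as chance imbalance and adjusts the treatment effect for it.

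The bias can go either way. If AB participants begin to walk more after seeing a manual centred on walking, the AB effect is underestimated, and success requires all three coprimary outcomes. If steps fall in AB, or rise in HEP (whose programme also covers physical activity), the effect is overestimated.

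**Working it through.** **1. Day count.** Set session 1 at day 0. Randomisation is at day -7 and the watch goes on between day -14 and day -7. If the baseline window is the first 7 days of wear:

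| Group baseline | Window days before day -7 | Window days on or after day -7 |
|---|---|---|
| day -14 | 7 | 0 |
| day -12 | 5 | 2 |
| day -10 | 3 | 4 |
| day -8 | 1 | 6 |
| day -7 | 0 | 7 |

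If the window is instead the last week before session 1, all 7 days fall on or after day -7 for everyone. Only a full 14-day lead combined with a first-7-days window lies wholly before randomisation.

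**2. The plan's power figure.** Inputs from Power Analysis: 104 completers per arm, difference 1000 steps, SD 2120, pre-post correlation 0.5, two-sided 0.05.

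- Change-score SD = 2120 × √(2 × (1 - 0.5)) = 2120.
- SE = 2120 × √(2/104) ≈ 294.
- Power is 92.5% by the normal approximation and 92.3% by the noncentral t with 206 df. The stated 92.3% is reproduced, so it is a change-score calculation.

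**3. Bias.** Let x be the amount by which the AB baseline mean is shifted relative to HEP in that week, with the post-test means unaffected.

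- Change score: bias = -x.
- Shared-baseline model: bias ≈ -βx, with β = correlation × SD(post)/SD(baseline) = 0.5 for equal SDs, so about -0.5x.
- Check: 4,000 simulated trials, using baseline-adjusted regression to stand in for the mixed model, with x = +200 and a true effect of 1000, gave a mean estimate of 903 against the expected 900.

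**4. Effect on power.** For the shared-baseline model, SE ≈ 2120 × √(1 - 0.5²) × √(2/104) ≈ 255. Power ≈ Φ(estimate/SE - 1.96). The values of x are assumptions.

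| x | Shared-baseline estimate | Power | Change-score estimate | Power |
|---|---|---|---|---|
| 0 | 1000 | 97.5% | 1000 | 92.5% |
| +100 | 950 | 96.2% | 900 | 86.5% |
| +200 | 900 | 94.2% | 800 | 77.7% |
| +300 | 850 | 91.6% | 700 | 66.3% |
| +400 | 800 | 88% | 600 | not computed |

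**5. Opposite direction.** With no true effect and x = -200, the shared-baseline bias is +100 steps. The chance of a significant result favouring AB rises from 2.5% to 1 - Φ(1.96 - 100/255) ≈ 5.9%.

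**The case against.** The strongest reply is that the documents leave the point open. No section says which 7 days are used, the 1 to 2 week range includes a lead that is wholly clean, the abstract puts randomisation after the baseline assessments, and the timeline figure is not available here. A reader might infer that baseline steps are collected after randomisation for every participant. The text does not establish that. What stands is that nothing in the text ensures the window closes first.

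A reader might also infer that the shared-baseline assumption fails. That would need a difference in walking between arms during the week, and there are real safeguards. Arms carry masked labels, the Fitbit starts only after session 1, and the first step goal uses data from the week after session 1. Pacing and mindful walking come in sessions 2 and 3. HEP participants also receive a manual and website with activity content. These reduce the likely size of x, but they do not withhold arm-specific content, so the guarantee from randomisation is still lost.

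Finally, a reader might pair shared-baseline estimates of 900 and 800 steps with the plan's change-score SE and report power of 86.1% and 77.3% (noncentral t). That mixes two analyses. For the planned primary model those estimates correspond to about 94% and 88%. The steeper losses belong to change-score analyses, such as the Wilcoxon sensitivity test, at x of +100 and +200.

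**Conclusion.** The point holds as a conflict between the stated schedule and the stated premise of the analysis. Pre-randomisation wear is 0 to 7 days, and the week named in the abstract can fall entirely after allocation. Equal baseline step means are therefore not guaranteed by randomisation, although nothing shows that they actually differ.

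Only the step-count coprimary is affected. The self-report measures and the walk test are described as done within the assessment period. The bias is about -0.5x in the primary model and -x in change-score analyses, of unknown sign. At x = +200 the primary model still has about 94% power, above the planned 92.3%; at x = +400 it has about 88%. These figures assume equal SDs, correlation 0.5, 104 complete pairs per arm and an unaffected post-test, and x itself is purely assumed. The plan's power figure and N of 260 are not in dispute. The correction is cheap, and as of March 2023 only 37 participants had been enrolled.

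**What to change.** 1. Define baseline steps as valid ActiGraph days before the date and time of the randomisation call, and make the abstract, ActiGraph and Randomization sections agree on this.
2. Hold the group baseline at least 8 days before the call. With the call at day -7, that is day -15 or earlier. Alternatively, hold the call, the website links and the manual until the 7-day window has closed.
3. For participants already randomised, keep the data as collected and add a sensitivity analysis for steps. It can use only date-stamped pre-randomisation days (baseline set to missing if the minimum is not met), relax the equal-baseline constraint, or do both.

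**Cost.** The lead-in is slightly longer. Consent at day -21 and a group baseline at day -15 leave about 6 days to mail the watch, so consent may need to move earlier too. Some early participants will have no clean step baseline. Read literally, trimming two days and keeping three needs five valid days, which a lead shorter than about 12 days cannot supply before day -7. The mixed model can handle a missing baseline, but such participants drop out of the change-score Wilcoxon test when it is restricted to pre-randomisation days. The sample size and stated power are unchanged.
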